#### **4.2.5 Analysis of other endpoints**

For secondary and exploratory endpoints, continuous data will be presented as means (SDs) or median (IQRs), as appropriate. The secondary endpoint followed no Gaussian distribution, will be presented as median (interquartile range) and tested by Mann-Whitney U test. POCD was defined as a 1 standard deviation decline in MoCA score on postoperative day 7, or at discharge if earlier, compared to baseline. This definition aligns with previous definitions of POCD and current recommendations for defining POCD or delayed neurocognitive recovery. [48,49] Mantel-Haenszel  $\chi^2$  and Cuzick tests assessed a potential dose-response relationship between the total hours of cognitive training and incidence of delirium. Analyses of delirium duration and delirium-positive days were conducted using the Zero-inflated Poisson regression model. Regarding the assessment of delirium severity, ordinal logistic regression model was used to model no delirium, delirium and severe delirium. Additionally, a post-hoc analysis incorporating study site, age, surgical technique, baseline educational level and cognitive function of the participants was conducted.

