### **3.7.3 Postoperative outcomes**

#### **The primary outcome:**

The incidence of delirium from postoperative day 1 to postoperative day 7 or before discharge, whichever occurred first.

Diagnosis of POD was based on the results of CAM or CAM-ICU twice daily, [42,43] specifically from 08:00 to 10:00 and from 18:00 to 20:00. All blinded researchers were trained in CAM/CAM-ICU assessment and the consistency among research members was reached. When there is a contradiction between the diagnosis obtained by the scale and the diagnosis of the psychiatrist, when there are still differences after consultation, the diagnosis of the psychiatrist shall prevail. In order to prevent missed diagnosis, we should communicate with the medical staff in the ward in time. After the patient is selected, the family member or escort staff should be informed, and the investigator should be informed of the evaluation of delirium in time when any abnormal performance of the patient's mood, consciousness, cognition and so on is found. Comprehensive reviews of progress notes, nursing documents, and medical records were conducted by blinded investigators to identify instances of delirium between postoperative day 1 and 7, employing a chart-based delirium identification instrument. [44,45] Patients diagnosed with delirium through any of the aforementioned methods were considered to have experienced delirium on that particular day. When postoperative delirium is found, the subject should communicate with the competent physician and decide on further diagnosis and treatment. If the patient's performance was normal 7 d after operation, the visit ended, while the patient with continuous delirium was followed up

until normal or discharged.

Outcomes were assessed by investigators specifically trained in recognition and assessment of delirium.

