**Secondary outcomes:**

- (1) cumulative incidence of POD
- (2) incidence of severe delirium, evaluated with the Memorial Delirium Assessment Scale (MDAS)[46]
- (3) postoperative cognitive dysfunction (POCD) on postoperative day 7 or at discharge if earlier, used by the Montreal Cognitive Assessment (MoCA) (range, 0 [worst] to 30 [best]), defined as a 1 standard deviation decrease from baseline in Montreal cognitive assessment score at postoperative day 7 or discharge.
- (4) cognitive function one month after surgery, used by the Revised Telephone Interview for Cognitive Status (TICS-m) (range, 0 [worst] to 50 [best])
- (5) 30-day all-cause mortality
- (6) durations of intensive care unit (number of days in the intensive care unit from the end of operation to discharge) and postoperative hospital care.
- (7) elapsed time from the end of surgery to delirium onset
- (8) duration of delirium (defined as the period between the first and last delirium-positive day, even if there were non-delirious days in between)
- (9) the total number of delirium-positive days in patients who developed delirium
- (10) cognitive function at three time points (baseline, preoperative, postoperative day 7 or at discharge if earlier. was used to assess early POCD on the seventh day after surgery or at discharge and cognitive function at any time points before or after surgery.
- (11) Postoperative intubation time, defined as duration from the end of the procedure to extubation.
- (12) intensive care unit readmission within 30 days after surgery.
- (13) Number of days alive and out of the hospital within 30 days. (The sum of the number of days patients were alive and not in the hospital within 30 days after surgery. It is calculated as 30 days minus the total number of days in hospital after surgery (maximum 30 days, minimum 0 days). If the patient is not hospitalized from 00:00 to 24:00 in a day, the number of days without hospitalization can be counted; After discharge, patients were hospitalized for a second time, and the second hospitalization time was also included in the total number of days in hospital. The patient died within 30 days of surgery. DAOH 30 is 0 days; If the patient was not discharged 30 days after surgery, DAOH 30 was recorded as 0 days.)

All outcomes were assessed by investigators masked to patient allocation.

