#### **General analysis:**

The data analyses mainly include statistical description and statistical inference. Quantitative data will be described by central tendency and dispersion tendency. The normally distributed data of central tendency and dispersion tendency will be described as means and standard division, respectively. The non-normally distributed data of central tendency and dispersion tendency will be described as median and quartiles. The qualitative data will be described as frequency and percentage. Statistical inference,

independent t test or non-parameter test will be used to compare the quantitative data between the two groups, while chi-square test or Fisher's exact test will be used for comparing the qualitative data between the two groups.

For missing data, imputation techniques were used. Statistical analyses were performed using SPSS 23.0 (IBM SPSS) and R (R software 4.2.1), and 2-sided  $P < 0.05$  was considered to be statistically significant in all statistical tests.

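### The zero-inflated Poisson model named for delirium duration and delirium-positive days does not assure a 5% error rate with its usual standard errors, and outcome 9 as defined has no zeros to inflate

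*Protocol*

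**What the plan says.** Section 4.2.5 of the protocol assigns one model to two secondary outcomes: "Analyses of delirium duration and delirium-positive days were conducted using the Zero-inflated Poisson regression model". Section 3.7.3 defines them differently. Duration (outcome 8) is "defined as the period between the first and last delirium-positive day, even if there were non-delirious days in between". Outcome 9 is "the total number of delirium-positive days in patients who developed delirium".

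Delirium is assessed "from postoperative day 1 to postoperative day 7 or before discharge, whichever occurred first", but section 3.7.3 adds an extension beyond day 7, "while the patient with continuous delirium was followed up" until recovery or discharge. Section 4.2.3 applies one threshold throughout: two-sided P<0.05 "was considered to be statistically significant in all statistical tests".

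The protocol gives no mean, variance or shape for either outcome. It names no variance estimator, dispersion check or fallback model for this analysis.

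**The concern.** A zero-inflated Poisson (ZIP) model has one extra parameter, which accounts for patients who never become delirious. Among the positive values it is still Poisson, so the mean fixes the variance. Nothing about a first-to-last span supports that link: two isolated positive days far apart score the same as continuous delirium between them. If the true spread is larger than the model assumes, standard errors are too small and P<0.05 is reached too often. If it is smaller, the test is too cautious and loses power. Either way the stated level and the confidence intervals cannot be relied on.

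Outcome 9 has a second problem. Every patient who developed delirium has at least one positive day, so the outcome as defined has no zeros, yet the named model exists to handle them.

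**Working it through.** **Inputs from the protocol.** Section 4.1 gives 35% delirium in controls, a 50% relative reduction (to 17.5%), 96 per arm, and 107 per arm after 10% dropout. The sample size reproduces: (1.96+0.8416)² × (0.35×0.65 + 0.175×0.825) / 0.175² = 95.3, so 96; and 96/0.9 = 106.7, so 107. The protocol states no figure for the ZIP analyses. With 107 per arm, an arm has about 107×0.35 = 37 or 107×0.175 = 19 delirious patients.

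**Assumed.** The shape of the durations, varied over days 1-7; the same shape and the same incidence in both arms (no effect).

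**Formula.** With treatment in both parts of the model, the positive values in each arm are fitted as a zero-truncated Poisson with mean m = λ/(1−e^(−λ)) and variance m(1+λ−m). Let R be the true variance divided by that model variance. The Wald test at 1.96 then rejects a true null with probability of about 2[1−Φ(1.96/√R)].

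**Two examples.**
- Half one-day, half spread evenly over 2-7 days: m = 0.5×1 + 0.5×4.5 = 2.75; variance = 0.5 + 0.5×139/6 − 2.75² = 4.52. λ = 2.531 gives a model variance of 2.75×(3.531−2.75) = 2.15. R = 2.10; 1.96/1.45 = 1.35; error about 18%.
- 25%, 50%, 25% on days 1, 2, 3: m = 2.00, variance 0.50. λ = 1.594 gives 2×(2.594−2) = 1.19. R = 0.42; 1.96/0.65 = 3.02; error about 0.3%.

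**Simulation.** 3,000 runs per cell, 96 and 107 per arm, incidence 35% and 17.5%; ranges over the four cells.

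| Assumed shape, days 1-7 | Mean | R | Formula | Model-based SE | Robust SE |
|---|---|---|---|---|---|
| Half one-day, half 2-7 | 2.75 | 2.10 | 18% | 16.3-18.4% | 3.9-4.9% |
| Strong right skew | 2.09 | 1.83 | 15% | 12.7-13.9% | 5.4-7.7% |
| Capped geometric, ratio 0.65 | 2.50 | 1.45 | 10% | 9.5-10.4% | 5.2-6.8% |
| Capped geometric, ratio 0.5 | 1.94 | 1.44 | 10% | 7.6-9.9% | 5.6-6.4% |
| Uniform | 4.00 | 1.09 | 6% | 5.6-6.5% | 5.1-5.6% |
| Humped | 3.89 | 0.77 | 2.5% | 1.8-2.8% | 5.0-6.6% |
| 40/40/20% on days 1-3 | 1.80 | 0.60 | 1.1% | 0.7-1.2% | 4.2-5.1% |
| 25/50/25% on days 1-3 | 2.00 | 0.42 | 0.3% | 0.1-0.3% | 4.7-5.4% |

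Poisson-like durations capped at 7 gave 3-5% with model-based errors. A direct numerical ZIP fit on five shapes agreed with this reduction. Coding duration as last minus first day, so that a one-day episode scores 0, left the pattern unchanged.

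**Outcome 8 against outcome 9.** Simulated day-by-day histories with gaps were scored both ways. Spans had R of 1.36-2.14 and error of 8-18%. Counts of positive days from the same histories had R of 0.75-1.07 and error of 2-6%. For an unbroken episode the two scores coincide, so outcome 9 is not immune, but the case for inflation is weaker.

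**Outcome 9 without zeros.** If only delirious patients enter, the inflation probability is driven to zero and an ordinary Poisson remains. For the geometric shape with mean 1.94 it puts e^(−1.94) = 14% of its mass on an impossible zero, and R becomes 1.61/1.94 = 0.83 instead of 1.44. The direction of the error thus depends on which population is meant.

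**The case against.** The strongest reply is that the protocol names a model and no variance estimator. Robust errors or a dispersion check may stand in the statistical analysis plan, which is not at hand, and the table shows that ZIP with robust errors behaves acceptably. This stands in part: the error rates above apply to model-based standard errors, and the absence of a check is not itself the finding. What remains is that the protocol fixes a Poisson variance for a span, and that its own definition of outcome 9 conflicts with the model assigned to it.

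Four stronger readings are tempting and are not supported:
- That false positives run at 10-19%. That is the upper part of a range set by an assumed shape; other plausible shapes give well under 5%.
- That the limited window causes the inflation. A bound lowers variance; the excess comes from long or scattered spans. Nor is seven days a strict limit, given the extended follow-up. In runs without a day-7 cut, onset-plus-persistence durations rose from 10-11% to 15-25%, but the protocol does not say whether later days count.
- That both outcomes are affected alike. The day-count simulations do not show it.
- That a rank test over all patients is the cure. Its level is sound under the null, but it asks another question: with identical durations and incidence of 35% against 17.5%, it rejected 78-80% of the time, largely repeating the primary endpoint.

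A missing offset for days observed is likewise no part of this point. Such detail can be left to the analysis plan, and length of stay is itself a post-randomisation outcome.

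**Conclusion.** The point holds in a conditional form. With the usual model-based standard errors, the ZIP count-part test does not assure its nominal 5% level for delirium duration. The error is about 10-18% for right-skewed or mixed durations, near 5% for uniform or Poisson-like ones, and about 0.1-3% for humped or concentrated ones. These figures rest on assumed shapes over days 1-7 and on 96-107 patients per arm; the protocol cannot settle which applies. For positive days the inflation is less well supported, but the mismatch between an outcome without zeros and a zero-inflated model is plain in the text. Two of 13 secondary outcomes are concerned. The primary χ² comparison is untouched.

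**What to change.** In section 4.2.5, keep a count model but state that its tests and intervals use robust (sandwich) or bootstrap standard errors. Robust errors gave about 4-7% across the shapes tried, and 7.7% at worst where skew was strong and delirious patients were few. Changing to a hurdle Poisson alone would not help, because its count part is the same zero-truncated Poisson.

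For outcome 9, reconcile sections 3.7.3 and 4.2.5. Fit either a zero-truncated count among delirious patients or a model over all modified intention-to-treat patients with zeros for the never delirious, and state which. If an all-patient rank test or mean-days comparison is added, label it total delirium burden, because it also reflects incidence.

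The cost is about one sentence of wording and no new data. Intervals may become wider or narrower, depending on the spread actually observed.

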### **5. Flow diagram of trial design**

[figure not shown]

## 6. Adverse events

### 6.1 Definition

Adverse events (Adverse Event, AE) refer to any adverse symptoms, abnormal signs and abnormal

laboratory results after the intervention study, whether or not there is a causal relationship with the intervention. Any adverse events, including those provided by the subjects voluntarily or obtained through inquiry by the investigator or by physical examination, laboratory examination or other examination methods, should be recorded on the CRF and actively handled, followed closely until remission or condition is stable.

## **6.2. Records of adverse events**

- (1) All adverse events must be tracked, and the investigator must record them in the corresponding section of the case report form and must record the adverse events in detail.
- (2) Adverse event content: name of symptom or sign or diagnostic name of disease or laboratory examination of an indicator abnormality.
- (3) Date of onset of adverse events: date of first occurrence of AE or related symptoms AE subjects.
- (4) End date of adverse events: date of cessation of AE or AE-related symptoms. If the AE still exists, do not fill in the end date.
- (5) Evaluation of the severity of adverse events a. Mild: symptoms and signs present, but can tolerate, generally without treatment; b. Moderate: symptoms or signs cause discomfort, daily activities are limited, appropriate treatment can be taken; c. Severe: no ability to work and daily activities, need active treatment.
- (6) Measures taken: a. discontinuation of the relevant medication or treatment; b. use of therapeutic measures; c. no measures taken.
- (7) End result of adverse events: persistence, improvement, mitigation.
- (8) Evaluation of the correlation between adverse events and intervention.

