### **8.3 Data Monitoring and Ethics Committee (DMEC)**

The DMEC will advise the Chairman of the Steering Committee if, in their view, the randomized comparisons have provided both (1) 'proof beyond reasonable doubt' that for all, or some, the treatment is clearly indicated or clearly contra-indicated and (2) evidence that might reasonably be expected to materially influence future patient management. Following a report from the DMEC, the Steering Committee will decide what actions, if any, are required. Unless the DMEC request cessation of the trial the Steering Committee and the collaborators will remain ignorant of the interim results.

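### The adverse-event end-result list in section 6.2(7) has no code for a fatal event, for recovery with sequelae or clearly for full resolution, and no serious-event field is named

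*Protocol*

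**What the plan says.** Section 6.1 defines an adverse event broadly, regardless of cause, and requires each one to be entered on the CRF and "followed closely until remission or condition is stable".

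Section 6.2 then lists what is recorded:

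- Item (1): every event, in detail.
- Item (4): the date the event ceased, with the exception "If the AE still exists, do not fill in the end date".
- Item (5): three severity grades. These are "Mild: symptoms and signs present, but can tolerate, generally without treatment"; "Moderate: symptoms or signs cause discomfort, daily activities are limited, appropriate treatment can be taken"; and "Severe: no ability to work and daily activities, need active treatment".
- Item (7): "End result of adverse events: persistence, improvement, mitigation".
- Item (8): the relation of the event to the intervention.

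Neither section defines a serious event or provides a field for one.

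Elsewhere, section 3.7.3 lists "30-day all-cause mortality" as secondary outcome (5). Section 3.2.3 makes death ahead of the primary outcome assessment a criterion for dropping a patient. Section 4.2.1 leaves patients whose operation was cancelled out of the modified intention-to-treat set. Section 8.3 asks the DMEC to advise whether "the treatment is clearly indicated or clearly contra-indicated".

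**The concern.** An end-result field should let each event finish in exactly one place. This one has no place for an event that ends in death or one that ends with residual damage, and it is unclear where a fully resolved event belongs. With no serious-event flag either, the named fields cannot yield a count of fatal or serious events by arm.

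The trial expects deaths, since it counts them as an outcome. At stake is whether a death can be tied to a specific event and to the relatedness judgement in item (8), and whether deaths that the mortality outcome may miss are coded anywhere. An SAP cannot repair this later, because it cannot analyse a category that was never collected.

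**Working it through.** The point rests on no sample size, power or event rate, so the check is a comparison of sections.

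**1. End-result list against the rest of section 6.** The possible courses of an event, set against 6.2(7):

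| Course of the event | Category in 6.2(7) | Supported elsewhere in section 6? |
|---|---|---|
| Unresolved | persistence | yes: blank end date under 6.2(4) |
| Better but not gone | improvement, perhaps mitigation | not separately |
| Fully resolved | none clearly; mitigation may be meant | yes: remission in 6.1, cessation date in 6.2(4) |
| Resolved with sequelae | none | no |
| Fatal | none | no; 6.2(4) has no end-date rule for death |

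Of 3 categories, 0 are fatal and 0 are with sequelae. Improvement and mitigation overlap and are not defined. The third row is an internal mismatch: an event that has stopped gets an end date but has no evident end result to go with it.

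**2. Other fields that might identify a fatal or serious event.** The severity scale in 6.2(5) stops at severe, with no life-threatening or fatal grade. No seriousness field is named. The detail required by 6.2(1) might appear as narrative, but narrative is not a code that can be tabulated by arm.

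**3. Does the mortality outcome fill the gap?** In part.

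- It counts deaths but does not link a death to an event or to the relatedness item 6.2(8).
- It is listed under postoperative outcomes. Training takes at least 10 days before surgery (3.2.1 and 3.3.2), so a death in that period precedes the window. That patient's operation would not take place, and under 4.2.1 cancelled operations leave the modified intention-to-treat set.
- A death ahead of the primary outcome assessment is a drop criterion in 3.2.3. The protocol does not say whether a dropped patient still counts towards mortality.
- A death after day 30 lies outside the window.

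For these deaths the adverse-event record is the natural source, and it has no fatal code.

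**The case against.** The strongest reply is that deaths are compared between arms whatever 6.2(7) says: all-cause mortality at 30 days is a secondary outcome, and days alive and out of hospital is set to 0 for a patient who dies. The CRF is not shown and may hold more fields, 6.2(1) demands detail, and no efficacy endpoint, analysis set or test uses the end-result field. All of this stands. It limits the point to coding, to linkage, and to deaths outside the mortality window or dropped from the data. It does not supply the missing categories.

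Some stronger readings are tempting but are not supported:

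- *Severity is graded by ability to work, so inpatients after CABG cannot be graded.* Item (5) grades the event. The mild and moderate definitions do not mention work, and the severe definition also needs loss of daily activities and a need for active treatment. A trivial event in intensive care fits mild. At most, the work and daily-activity wording of the severe grade suits patients just after CABG poorly.
- *Lasting harm cannot be recorded.* Persistence with a blank end date records an unresolved event. What is absent is a separate category for recovery with sequelae.
- *A fatal event must be entered as persistence.* The protocol does not say how a fatal event is coded, and item (4) does not say that it counts as still existing.
- *The adverse-event table will contradict the mortality result, or the DMEC will lack what it needs.* The protocol describes no such table, and section 8.3 does not restrict the DMEC to the coded event fields.

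**Conclusion.** The point holds as a minor correction to safety recording. The list in 6.2(7) has no fatal and no with-sequelae category and no clear resolved category, it does not match 6.1 and 6.2(4), and no serious-event field is named. As described, the record cannot code a fatal event as fatal or support a table of fatal events by arm with relatedness. The mortality outcome covers this only in part.

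The size is 0 of 3 categories fatal or with sequelae. The documents give no mortality rate, so a number of miscoded deaths cannot be derived, and the point does not need one. Two assumptions apply: that the CRF follows the list in section 6.2, and that the 30-day mortality window starts at surgery, as its place among the postoperative outcomes implies. If the CRF already has fuller categories, only the protocol text needs correcting. The primary comparison of delirium is unaffected.

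**What to change.** 1. Replace the list in 6.2(7) with: resolved; resolved with sequelae; improving; not resolved; fatal. State in 6.2(4) that the end date of a fatal event is the date of death.
2. Add one yes/no field for a serious event, with its definition, to section 6.2 and the CRF.
3. Reconcile fatal codes with the 30-day mortality outcome. List separately deaths that fall before surgery, after day 30, or in patients dropped under 3.2.3.
4. Tabulate fatal and serious events by arm, with relatedness, for all randomised patients, including those whose operation was cancelled and those who were dropped.

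The cost is one CRF page and a few lines of section 6.2. The downside is that events already entered need recoding. The efficacy analyses do not change.
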